### Intervention {11a}

#### Explanation for the choice of comparators

Under the stepped-wedge design framework, communities that will function as a control group will not receive any intervention at the moment of their first measurement. Groups will be compared in a parallel fashion at the same calendar study period, the distinctive feature of study groups is time of exposure to the program, and the group that has not yet been exposed to the program will function as a control group for comparisons at a given study calendar time (see Table 1). Due to ethical considerations, every child, who is diagnosed with undernutrition, anemia, obesity, or developmental delays, will be referred for further assessment and remedial services, regardless of group assignment or program participation status.

#### Intervention details

The NPECDP-UKA is one of the three components constituting UKA’s Integral Model of Early Child Development. The other two components focus on improving physical development of young children and fostering community development, respectively.

#### NPECDP-UKA

UKA will implement an integrated responsive parenting nurturing care approach to promote different child development domains, i.e., motor, language, cognitive, and social. Workshops on appropriate responsive parenting practices will encourage nurturing interactions between parents and/or other caregivers with children, from pregnancy and up to 60 months of age. These workshops are supported by two sets of manuals: the first one is an unpublished pedagogical support guide for the facilitators to deliver program in a standard way, and the set contains the workshop materials needed to support the facilitator’s counseling to families. The model promotes play as a form of learning and addresses responsive parenting skills for healthy feeding, sleeping, soothing, and physical to promote self-regulation of behaviors and emotions.

#### Physical development component

UKA will promote a healthy, balanced, and varied diet and encourage the consumption of locally available foods. Standardized workshops and advice will be implemented to provide guidance on optimal health and nutrition for preschool children (i.e., under 5 years of age). These workshops include a neurodevelopment component and a responsive nurturing care component which covers four dimensions: feeding, sleep, movement, and self-regulation. As part of this component, the implementation team will monitor weight, height, or length, quarterly. Whenever signs of malnutrition are identified, caregivers will be referred to clinical services that may include provision of vitamin supplements and malnutrition recovery advice. Infectious diseases such as diarrhea and acute respiratory infections will also be monitored, and appropriate referrals will be made for clinical services including oral rehydration and counseling on proper hygiene practices. During pregnancy, iron and micronutrient supplementation may be provided if warranted. A comprehensive counseling model will be overseen by community commissioners―contracted by UKA and trained and supervised by the research team―who support the project as translators and interpreters for situations where beneficiaries speak an indigenous language and are not fluent in Spanish. Women will be provided personalized advice during their last trimester of pregnancy and during the first month postpartum. Every 3 months, hemoglobin will be measured in a capillary blood sample for the diagnosis and timely treatment of anemia in pregnant women and children between 6 months and 5 years of age. Treatment of anemia for pregnant women will be iron and folic acid supplementation. Micronutrients will be provided for children at risk of anemia, and prophylactic treatment based on iron will be also provided for children.

#### Community development component

This component has two sub-components. The first addresses household food insecurity. The UKA team will promote access and availability of fresh, healthy, and nutritious food to improve the diet of families with children under 5 years and pregnant women, through local food production based on sustainable community and family farming models. The second sub-component centers around UKA’s effort to provide access to basic WASH services needed for proper ECD including dry ecological toilets, access to water with rainwater collection systems, safe water storage and water purification systems, sludge water treatment systems, and environmentally friendly energy efficient friendly stoves that save wood and decrease the emission of air born pollutants inside the home.

#### Criteria for discontinuing or modifying allocated interventions

The criteria for discontinuing or modifying allocation of communities will be sudden inaccessibility to the community due to external problems such as public insecurity or refusal to participate from local authorities.

#### Strategies to improve adherence to interventions

All training facilitators will participate in training and face-to-face sensitization activities in order to ensure fidelity of program implementation. In order to improve participation rates, before each training program delivery workshop, participants will receive a telephone reminder. During the trial, adherence will be monitored at the beginning and end of each program session.

#### Relevant concomitant care permitted or prohibited during the trial

There are no restrictions on the involvement of participants who receive other interventions such as government programs. We expect that such exposure will be similarly distributed over study groups under random allocation. In case unbalances in this characteristic are detected, participation in other inventions will be adjusted for in analyses.

#### Provisions for post-trial care

The NPECDP-UKA will continue indefinitely after the impact evaluation concludes, but it can be modified as a result of the study to improve its effectiveness.

### Outcomes {12}

#### Primary outcome measures

The primary outcomes of the study are the ECD domains assessed through the Child Development Evaluation Test 2nd Edition (CDE-II). The CDE-II, or *Evaluación del Desarrollo Infantil* (EDI-II) in Spanish, was developed and validated in Mexico to screen populations for risk of developmental delays in early childhood. The test has specific items for fourteen age groups of children aged 1–60 months. ECD domains assessed included gross motor, fine motor, language, social, and cognitive skills. The CDE-II is based on age-group specific items, and score results are categorized into three levels following a traffic light interpretation: green (normal development), yellow (developmental lag), and red (at risk of development delay). These three categories will be used as the specific measurement variable, the analysis metric will be the final value (by ECD domain), and the method of aggregation will be the proportion of children falling within each traffic stoplight category. EDI-II will be carried out according to its application guidelines [24, 25], by trained, standardized, and certified research personnel.

#### Secondary outcome measures

Our secondary outcomes will be child nutritional status and ECD measured assessed through two additional instruments.

#### Nutritional status

Length/height-for-age, weight-for-age, and hemoglobin measurements will be used to assess children’s nutritional status. Anthropometric measurements will be made by trained personnel and standardized according to international protocols [26, 27], using SECA digital scales (874 TM) with an accuracy of ±50 g and SECA portable stadiometers (217 TM) with an accuracy of ±1 mm. After applying data cleaning procedures [28] and following the WHO reference standards [29], our main suboptimal nutritional development indicator will be chronic undernutrition or stunting defined as a length (or height) for age *Z* score below −2.

#### ECD measured through the Bayley Scales of Infant and Toddler Development, Third Edition (BSID-III)

This is a diagnostic test that consists of the following scales: 1) cognitive scale, assesses the child’s non-verbal responses and measures learning processes, problem solving ability, attention, the ability to count and classify objects, and the ability to play 2). Language and communication scale, which includes the subscales to assess receptive and expressive language. The first subscale measures the child’s ability to understand different stimuli, words, or instructions. The second subscale assesses language development through vocalizations, word use, and sentence construction 3). Motor scale, which includes a fine motor subscale that measures hand-eye and hand-to-finger coordination and the gross motor subscale that measures the child’s control over his or her body and abilities to move the torso and limbs 4). Social-emotional scale, which assesses the main milestones of social-emotional development, such as self-regulation, attention, child’s ability to relate to and interact with family members and strangers, among other temperamental and social aspects. These scales are administered and scored independently, resulting in domain-specific assessments. The cognitive, language, and motor scales are assessed through direct observation of the child’s abilities on various items that are ordered in an ascending order of difficulty. The socio-emotional scale comprises thirty-five questions with five Likert-scale-like response points answered by the caregiver.

The BSID-III will be applied in a subsample of children from the group conformed by the first set of communities exposed to the program (group A) and its comparison group of children from caregivers who refused to participate in the study but live in the same communities (i.e., quasi-experimental analyses). Additionally, the BSID-III will be applied in a subsample of group B during its baseline assessment period, i.e., before any NPECDP-UKA exposure occurs. These data will be compared to the subsample of children from group A at their third follow-up, i.e., once they had been exposed for 12 months to the NPECDP-UKA. The BSID-III will be applied to children aged 1 to 42 months.

A concurrent validation using data from children with both BSID-III and CDE-II measures will also be performed.

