**Table 1 Tab1:**
[figure not shown]
Study groups, exposure times, and age of children

The main feature of the proposed design is the possibility of comparing groups of children at the same age range but with a different time of exposure to NPECDP-UKA, at the same calendar period. This design feature will allow to eliminate potential confounding cohort effects since children with the same age across study groups will also share the same year of birth. Table 1 shows the age range of children for each study group at different study calendar periods. The upper age limit of the ECD assessment will be 60 months; therefore, the first group of communities to be exposed to the program will include children aged 1–30 months at their first assessment and these children will be aged 31–60 at their final assessment. At given calendar periods (*t* = 2, 4, 6), the group unexposed to the intervention will function as a control group. For example, the last group of communities to be incorporated to the study (group D) will function as a control group at the last calendar period (*t* = 6). This will allow to estimate the effect of NPECDP-UKA on ECD for exposure times of 30 months (group A vs group D), 24 months (group B vs group D), and 12 months (group C vs group D). Given the rapid changes at early ages and considering the first thousand days of life as a critical opportunity window, we consider that the planned exposure times are adequate to detect changes as well as a gradient of the effect with respect to time exposure. Comparisons between groups will be performed cross-sectionally for children of the same age range. There will be a total of six calendar periods, with a time span of 6 months between the mid-point of consecutive periods and an approximate time span of 6 months between consecutive individual measurements.

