### Participant timeline {13}

Table 2 shows the chronogram of study activities including intervention implementation schedule across study groups and the corresponding measurements of ECD and nutritional status outcomes among pregnant women and children. The number of repeated measurements across time will depend on the timing when each group starts being exposed to the intervention.

**Table 2 Tab2:** Chronogram of study activities and measurements of child development scales

Activities	Study calendar period						
	t0	t1	t2	t3	t4	t5	t6
Community’s allocation	X						
Eligibility in communities A		X					
Enrollment in communities A		X					
Measurement in communities A*		X	X	X	X	X	X
Eligibility in communities B			X				
Enrollment in communities B			X				
Measurement in communities B*			X	X	X	X	X
Eligibility in communities C					X		
Enrollment in communities C					X		
Measurement in communities C*					X	X	X
Eligibility in communities D							X
Measurement in communities D							X
Measurement of CDE-II		X	X	X	X	X	X
Measurement of MSCA							X
Measurement of BSID-III		X	X	X			
Nutritional status assessment		X	X	X	X	X	X

*Intervention starts right after their first measurement. There will be a time span of 6 months between the mid-point of consecutive periods and an approximate time span of 6 months between consecutive individual measurements

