The stepped-wedge design has been proposed for tackling limitations of classical designs when a control group is not feasible given ethical or logistical considerations [20]. Our design corresponds to a specific stepped-wedge design where effects are assessed as in a parallel design. The main feature of this design is the sequential incorporation of study groups; the defining characteristic of study groups is the time of exposure to an intervention. The assignment of experimental units to study groups is randomized and evaluation can be performed at the same calendar period across study groups; this characteristic precludes effects from time of measurement to be confounded with intervention effects. An alternative version of the stepped-wedge design proposes comparing measurements of the same group before and after intervention; since this occurs in different calendar times, confounding due to period effects cannot be ruled out under this setting [20].

Another type of confounding relates to age; given the nature of ECD outcomes, it is key to compare intervened and not intervened subjects at the same ages. This guarantees that the very same items from ECD scales are used to assess intervention effects. On the other hand, changes in child development at early ages occur very rapidly. This characteristic of ECD complicates using classical estimators such as the difference in differences estimator mainly for three reasons: (1) at the individual level, it is difficult to interpret changes when assessment items vary with age; (2) time differences between measurements across study groups are required to be balanced to avoid confounding; and (3) the distribution of initial ages should also be balanced across study groups. Although these imbalances may be attenuated by using adjustment covariates in models, it would be preferable to avoid these sources of potential bias with a robust design.

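### The only planned BSID-III comparison between randomised groups sets group A at t3 against group B at t2, so calendar period is aliased with exposure

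*Protocol article*

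**What the plan says.** Under Outcomes, the BSID-III subsection plans two effect comparisons. One is within group A, between enrolled children and children whose caregivers declined; it is quasi-experimental. The other is between randomised groups. Its control data come from group B while still unexposed: "the BSID-III will be applied in a subsample of group B during its baseline assessment period". Its exposed data come from group A: "These data will be compared to the subsample of children from group A at their third follow-up". The article equates that visit with a year on the programme. No age range, adjustment or exception to the general comparison rule is given for it, apart from the instrument's overall limits of 1 to 42 months.

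The general rule is in Design and setting {9}, in the text under Table 1, which names as the main feature of the design "comparing groups of children at the same age range but with a different time of exposure to NPECDP-UKA, at the same calendar period". The section on the choice of comparators repeats the same-period rule. Sample size {14} repeats both the same-period and the same-age rule.

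**The concern.** The BSID-III comparison between groups appears to step outside the rule on which the design relies. If the exposed arm is measured one period later than the control arm, anything that changes between the two rounds (season, assessor practice, outside events) becomes part of the estimated effect. The alignment of birth cohorts, which the article presents as a benefit of the design, goes as well.

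BSID-III is the article's diagnostic instrument at the younger ages, and this is its only contrast between randomised groups. A biased estimate here could be read as experimental confirmation of the CDE-II screening results. The article itself lists exogenous shocks as a limitation, and Trial status reports that recruitment was suspended in March 2020.

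**Working it through.** **Inputs**
- Table 2, group A row: "Measurement in communities A* X X X X X X", starting at t1. Group B row: "Measurement in communities B* X X X X X", starting at t2. BSID-III row: "Measurement of BSID-III X X X", that is t1, t2 and t3.
- Table 2 footnote: exposure starts directly after a group's first measurement, and periods are 6 months apart. Enrolment of group C is at t4; group D is measured at t6.
- Design and setting {9}: group A is aged 1–30 months at its first assessment.
- Sample size {14}: about 150 children per 6-month age band; n = 900 for group B versus group D.

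**Step 1: reproduce the plan's exposure figures.** Exposure = 6 × (period − start period). At t6: A = 6 × 5 = 30, B = 6 × 4 = 24, C = 6 × 2 = 12, D = 0 months. These match the article. For group A, 12 months gives 6 × (t − 1) = 12, so t = 3.

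**Step 2: line up the periods.** Group A's age range at period t is 1 + 6(t − 1) to 30 + 6(t − 1).

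| Period | Group A age (months) | Group A exposure (months) | Group B |
|---|---|---|---|
| t1 | 1–30 | 0 | not yet measured |
| t2 | 7–36 | 6 | baseline, unexposed |
| t3 | 13–42 | 12 | 6 months exposed |
| t4 | 19–48 | 18 | 12 months exposed; BSID-III has ended |

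The planned contrast is A at t3 against B at t2, a gap of one 6-month period.

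**Step 3: can analysis repair it?** Statistical methods {20a, 20b, 20c} allow regression on unbalanced observed characteristics, which could handle age. Period is constant within each arm and differs between arms, so it is collinear with exposure and cannot be adjusted for. A child of age a in group A was born at t3 − a, and one of the same age in group B at t2 − a, which is 6 months earlier. Matching on age therefore leaves both period and birth cohort unaligned.

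**Step 4: ages.** Table 1 is not shown, so group B's range is inferred: 900 / 150 = 6 bands = 36 months, hence 25–60 months at t6 and, 24 months earlier, 1–36 months at t2. Against A at t3 (13–42), the shared range is 13–36. If the full ranges were used, the mid-range ages would be 27.5 and 18.5 months, a gap of 9 months. With group B limited to 7–36, the gap would be 27.5 − 21.5 = 6 months.

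**Step 5: is there a contemporaneous alternative?** At t2, A (7–36 months, 6 months exposed) can be set against unexposed B at the same ages. At t3, B already has 6 months of exposure, and C and D enter only at t4 and t6, after BSID-III ends. A contemporaneous randomised 12-month contrast with an unexposed group is therefore not available in this schedule.

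**The case against.** The strongest defence concerns age. The BSID-III subsection gives no age range for these subsamples, and the general same-age rule can be read as limiting the analysis to 13–36 months. The article does something similar when it illustrates A versus B at t2 in children of 7 to 36 months. A reader might infer that the plan definitely compares children of different ages. The documents do not establish that: the full-cohort ranges need not apply to subsamples, and group B's range is back-calculated. This part of the defence stands, but it leaves the calendar gap untouched.

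A reader might also infer that randomisation is lost. It is not. Communities are randomised within blocks, so balance of community characteristics survives; what is lost is alignment of period and birth cohort.

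The Discussion says "since this occurs in different calendar times, confounding due to period effects cannot be ruled out under this setting", but that sentence is about before-and-after comparisons within one group. It applies here only by analogy. The direct conflict is with the design, comparator and sample size sections.

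The March 2020 suspension does not show that bias occurred. Trial status does not say when t2 and t3 took place or whether outcomes changed.

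The literal reading of third follow-up as t4, with 18 months of exposure, does not hold either. The same sentence gives 12 months and BSID-III stops at t3, so it is a labelling slip.

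Finally, the planned contrast has a purpose: it is the only randomised route to a 12-month BSID-III effect. The comparison of enrolled and declining families within group A is contemporaneous, but it is not randomised. That is a reason to keep the planned contrast as supportive, not as the main one.

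**Conclusion.** The concern holds for calendar period and birth cohort. The single randomised BSID-III contrast is offset by one 6-month period, contrary to the article's own comparison rule. Period is fully aliased with exposure, so its effect cannot be separated from that of the programme by any adjustment. The size and direction of the resulting bias cannot be derived from the documents.

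The age mismatch is conditional. It arises only if the general same-age rule is not applied, and its size (13–42 against about 1–36 months) rests on full-cohort ages and on the inference from n = 900 at 150 per band.

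This should be fixed but is not critical: BSID-III is a secondary outcome measured in subsamples, communities remain randomised, and the primary CDE-II comparisons and Table 3 do not depend on it.

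**What to change.** 1. Make group A versus group B at t2, ages 7–36 months, the main randomised BSID-III contrast. Table 2 schedules BSID-III at t2 but does not say which groups that round covers, so confirm that it includes group A.
2. Keep group A at t3 versus group B at t2 as a supportive analysis, restricted to 13–36 months, adjusted for age and labelled non-contemporaneous, with a statement that period and birth-cohort effects cannot be excluded.
3. Replace the label third follow-up with third measurement (t3).

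If group A is already assessed with BSID-III at t2, the cost is protocol wording only; if not, a subsample would have to be added at that round. The scientific price is that the contemporaneous contrast reflects 6 rather than 12 months of exposure. The within-group-A comparison at 12 months remains as non-randomised supporting evidence.

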### ECD measured through McCarthy Scales of Children’s Abilities (MSCA)

An adapted version in Spanish of the original version of the MSCA [30] will be used. This test includes five scales to assess diverse ECD domains: Verbal, Quantitative, Executive-Perceptual, Memory, and Motor. The combination of the first three scales provides a General Cognitive Index (GCI), which is considered equivalent to the IQ. The test will be applied to children from 42 to 60 months of age.

